**Methods/analysis:**

7 wards from 2 hospitals will progressively incorporate the intervention into daily practice over 14 months. Wards will adopt HEADS-UP in a pragmatic sequence, guided by local clinical enthusiasm. Initial implementation will be facilitated by a research lead, but rapidly delegated to clinical teams. The primary outcome is excess length of stay (a surplus stay of 24 h or more, compared to peer institutions’ Healthcare Resource Groups-predicted length of stay). Secondary outcomes are 30-day readmission or excess length of stay; in-hospital death or death/readmission within 30 days; healthcare-acquired infections; processes of escalation of care; use of traditional incident-reporting systems; and patient safety and teamwork climates. HEADS-UP will be analysed as a stepped wedge cluster controlled trial. With 7840 patients, using best and worst case predictions, the study would achieve between 75% and 100% power to detect a 2–14% absolute risk reduction in excess length of stay (two-sided p<0.05). Regression analysis will use generalised linear mixed models or generalised estimating equations, and a time-to-event regression model. A qualitative analysis will evaluate facilitators and barriers to HEADS-UP implementation and impact.

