**Figure 3 BMJOPEN2014007510F3:**
[figure not shown]
HEADS-UP (Hospital Event Analysis Describing Significant Unanticipated Problems) stepped wedge cluster design.

The order in which clusters receive the intervention will be guided by logistical restrictions, and the de facto recognition of clinicians enthusiastic to introduce HEADS-UP to their wards. Although cluster randomisation (randomising the order in which the clusters receive the intervention) would be preferable, it is important to recognise the impact of willing early adopters who then lead their colleagues in implementing the intervention.^30^ They are likely to participate more extensively and follow through more rigorously and enthusiastically with the intervention than units at later stages of the intervention diffusion.^31^ Sufficient leadership and support from these early adopters will be needed to maximise the use of HEADS-UP in all the desired areas, much as the introduction of surgical checklists, for instance, has historically relied on strong clinical leadership.^32^ HEADS-UP is introduced to new clusters at two-monthly intervals.

The study is conducted at two sites. The first is a university-associated community general hospital. Clusters from this site are generated from the acute admissions and downstream medical (gastroenterology, respiratory and geriatric) wards. Each cluster comprises clinical areas that are physically linked, served by the same medical team, or both. This will help to limit contamination between groups. The second site is an academic hospital, where HEADS-UP will be implemented within the geriatric wards.

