### Sample size, power calculation and analysis

In the 33 months preceding the study, local data from six of the seven anticipated clusters described a median of 522 patients matching our inclusion/exclusion criteria each month (range 316–722). Mean eLOS rates ranged from 5.6% to 51.5%.

Cluster controlled trials also require an estimation of the intraclass correlation coefficient (ICC); this is complex, and observed ICCs rarely match their predicted values. ICC estimation should take into account the results of previous studies, as well as the anticipated numbers of individuals and clusters in the index study. Greater numbers of individuals in a study reduce the width of the ICC confidence interval, mitigating the effect of a relatively small number of clusters.^53^ In addition, clinical outcome measures tend to have lower ICCs than process measures.^53^ The observed ICC for falls in a multifactorial intervention on elderly care wards was only 0.007.^54^ However, ICCs for length of stay and appropriateness of stay in trials of inpatient care pathways were an order of magnitude higher.^55^ We therefore adopted the more conservative ICC estimate of 0.06. In any case, the power under a stepped wedge cluster randomised trial is relatively insensitive to ICC underestimation, compared to a parallel cluster design.^56^ Similarly, stepped wedge trial power is relatively insensitive to variations in the coefficient of variation.^57^ In addition, in our best-case prediction the coefficient of variation approached the level at which adjusting for variable cluster size has a negligible impact on sample size, even in parallel cluster trials.^58^ No adjustment for coefficient of variation was therefore required.

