Given the variation in baseline outcomes in our local data set, we then estimated the study's power to detect a 1 standard deviation reduction in eLOS on the wards with the highest and lowest baseline outcome rates. With 7840 patients in the trial (560 patients/month), and two-sided p<0.05, the study would achieve 100% power to detect a 14% absolute risk reduction. At worst, in the ward with the lowest baseline outcome rate, it would achieve 75% power to detect a 2.3% absolute risk reduction. We therefore propose that the study's power to detect a 2–14% absolute risk reduction lies between 75% and 100%. With this complex trial design, statistical uncertainty in power calculations is not unusual. The recent protocol of a large stepped wedge cluster randomised trial similarly produced a range within which its power might lie.^29^ Experts also advocate more widespread recognition of the inherent limitations of statistical power thresholds.^59^

The stepped wedge design compares outcomes in each cluster before and after the introduction of the intervention. Overall differences in outcomes between preintervention and postintervention periods will be reported. Primary analysis will be on an intention-to-treat basis, with a separate prespecified per-protocol analysis of those units implementing the intervention with high fidelity. Analyses will use the patient-level data described above, clustered within ‘units’, using random effects to model the correlation between individuals within the same cluster. Generalised linear mixed models, or generalised estimating equations, will form the basis of the analysis.^57^ Results will also be assessed using a time-to-event regression model. Underlying temporal trends (including seasonal trends) will be accounted for. We will evaluate any interaction effect between intervention group and ‘duration of HEADS-UP implementation’ to see if the intervention exerts an incremental effect over time. There will be a prespecified analysis excluding patients coded for palliative care, to further isolate the effect of the intervention. Sensitivity analyses will judge whether primary outcome results remain unchanged when other patient groups (eg, those spending less than 50% of their stay on the specified ward) are included. No interim analyses are planned, nor is a formal health economics analysis.

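### On seven wards the plan leaves GLMM or GEE open: uncorrected GEE rejects a true null about 14–18% of the time, and a ward-intercept model holds 5% only if wards do not drift

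*Protocol article*

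**What the plan says.** The analysis text is in the protocol article under Sample size, power calculation and analysis. It describes a patient-level analysis "using random effects to model the correlation between individuals within the same cluster", and then says: "Generalised linear mixed models, or generalised estimating equations, will form the basis of the analysis". It promises adjustment for temporal and seasonal trends. It does not choose between the two methods. It names no small-sample correction, no reference distribution and no ward-by-period term, and it rules none of these out.

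The design is small in clusters. The abstract says: "7 wards from 2 hospitals will progressively incorporate the intervention into daily practice over 14 months". Study design and setting adds: "HEADS-UP is introduced to new clusters at two-monthly intervals".

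The only remark on the number of clusters is in the paragraph on the intraclass correlation. Large patient numbers are said to narrow its confidence interval, "mitigating the effect of a relatively small number of clusters".

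**The concern.** The two methods are offered as interchangeable, but with seven wards they are not.

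- **GEE.** Its usual robust standard error is estimated from variation between clusters, and there are only seven.
- **GLMM.** If the only random effect is a ward intercept, two patients on a ward are taken to be equally correlated whether they were admitted in the same week or a year apart. Shared period terms remove change common to all wards. They do not remove change particular to one ward, and in a stepped wedge each ward's own before-and-after contrast carries most of the information.

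The primary p-value and confidence interval are at stake. If the analyst takes the standard form of either option, the nominal 5% may not be the real error rate. The two sentences quoted on the model also do not describe one method, because GEE has no random effects. The reader therefore cannot tell which error rate applies.

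**Working it through.** **Inputs from the protocol article**

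- Seven wards, 14 months, a step every two months. The layout figure is not shown, so layouts of 7 and 8 two-month periods were both tried.
- Size and level: "With 7840 patients in the trial (560 patients/month), and two-sided p<0.05". This is 7840/7 = 1120 patients per ward.
- Correlation: "We therefore adopted the more conservative ICC estimate of 0.06".
- Ward rates of excess length of stay from 5.6% to 51.5%.

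**Assumed, because the document gives no figure:** ward-specific drift, set as independent ward-by-period effects with SD 0, 0.1, 0.2 or 0.3 on the logit scale.

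**Step 1: reproduce the stated power.** The Hussey-Hughes variance for a ward random intercept plus fixed period effects is

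var = I·s²(s² + T·τ²) / [(I·U − W)s² + (U² + I·T·U − T·W − I·V)τ²]

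Here I is the number of wards, T the number of periods, U the number of treated ward-periods, and W and V the sums of squared column and row totals. With 7 periods and 160 patients per cell, I = T = 7, U = 28 and W = V = 140.

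- At 5.6%: total variance 0.056 × 0.944 = 0.05286; τ² = 0.06 × 0.05286 = 0.003172; s² = 0.94 × 0.05286/160 = 0.0003106.
- Numerator 7 × 0.0003106 × 0.02251 = 0.00004894. Denominator 56 × 0.0003106 + 196 × 0.003172 = 0.6391. Hence var = 0.0000766 and SE = 0.00875.
- Power = Φ(0.023/0.00875 − 1.96) = Φ(0.67) = 74.8%, against 75% stated. With 8 periods and 140 per cell it is 74.0%.
- At 51.5% with a 14-point reduction, power is 100%, as stated.

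The stated power therefore matches a model with a constant ward intercept, no ward-specific drift and a normal reference.

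**Step 2: why uncorrected GEE fails here.** With period indicators and the intervention there are 8 or 9 fixed parameters (7 + 1 or 8 + 1). The seven ward score contributions sum to zero at the solution, so the middle matrix of the sandwich has rank at most 6. The robust standard error is then biased downwards.

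**Step 3: simulated false-positive rates (%) at nominal 5%.** 8 periods with period effects, N = 7840, 1,900 replicates per row. Ward variance on the latent scale is (0.06/0.94) × π²/3 = 0.21, around an assumed 25% rate.

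| Ward-by-period SD | GEE uncorrected, z | GEE uncorrected, t(5) | GEE Fay-Graubard, t(5) | GEE Mancl-DeRouen, t(5) | Ward-intercept GLMM, z |
|---|---|---|---|---|---|
| 0 | 15.4 | 7.5 | 5.1 | 2.5 | 5.1 |
| 0.1 | 17.8 | 8.6 | 5.5 | 2.8 | 9.3 |
| 0.2 | 15.6 | 7.9 | 5.0 | 2.5 | 17.0 |
| 0.3 | 15.8 | 7.7 | 5.1 | 2.5 | 28.3 |

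GEE here has exchangeable working correlation. The Monte Carlo standard error is √(0.05 × 0.95/1900) = 0.5 points near 5% and about 1.0 point near 28%.

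**Step 4: other settings and repeat runs (500 to 2,000 replicates)**

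- *Uncorrected exchangeable GEE:* 13.5–18.3% with period effects, 11.5–14.4% with linear time, and 14–17% with linear plus seasonal terms. With independence working correlation it is 17–22%.
- *Ward intercept only:* 4–6% without drift, then about 6–9%, 16–19% and 27–31% at SD 0.1, 0.2 and 0.3. The highest values come from a version with fixed ward effects.
- *Other shapes of drift, ward intercept only:* linear ward slopes of SD 0.3 and 0.6 give 6.5% and 14.3%. Random walks of SD 0.1 and 0.2 per period give 11.3% and 25.7%.

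For scale, SD 0.2 at a 25% rate is 0.2 × 0.25 × 0.75 = 3.75 percentage points between periods, with a latent cluster autocorrelation of 0.21/(0.21 + 0.04) = 0.84.

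**Step 5: what repairs it**

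- *Ward-period overdispersion with a t reference:* 3–8% across settings. Residual degrees of freedom are 56 − 7 − 7 − 1 = 41 for 8 periods and 49 − 7 − 6 − 1 = 35 for 7.
- *Ward-by-period random effect with a normal reference:* 5.1% without drift but 9.5% at SD 0.2 (16.1% in the same run without the term). The added term alone is not quite enough.

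**The case against.** The strongest reply is that these rates belong to implementations the protocol never commits to. Variance corrections and reference distributions are commonly left to an SAP, which is not shown, and a journal article condenses its protocol. Much of this stands, and it rules out several stronger readings:

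- *That GEE cannot hold 5% on seven wards.* The inflation belongs to the uncorrected sandwich. Fay-Graubard with t(5) gives 5.0–5.5% in the table above and 3.5–6.8% over all settings. Mancl-DeRouen is conservative, at about 2–3% in most settings.
- *That the plan specifies a ward intercept and nothing else.* Its wording also fits a ward-by-period term.
- *That the trial carries a 15–30% false-positive risk.* This joins the uncorrected-GEE figure to the larger assumed drifts. The article mentions staff and policy changes as general background, and site or systemic change as a limitation, but quantifies no ward-specific drift. An outcome measured against predicted stay, and the casemix, occupancy and workload data to be collected, might absorb some of it.
- *That the protocol claims many patients make up for few wards in the test.* The sentence containing "mitigating the effect of a relatively small number of clusters" concerns the precision of the intraclass correlation. It says nothing about the error rate and does not contradict this point.

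The reply does not remove the point. The article itself puts forward the two methods as equal bases for the primary analysis. In standard form and with no drift at all, one gives about 15% and the other about 5%.

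**Conclusion.** The point holds as a conditional one. With seven wards, GEE in its standard uncorrected form with period effects has a false-positive rate of about 14–18%, and this needs no assumption about drift. A ward-intercept-only model is sound at about 5% without drift. It rises to about 6–9%, 16–19% and 27–31% at assumed ward-by-period SDs of 0.1, 0.2 and 0.3. The plan has not chosen either form; the defect is that it permits both without addressing few clusters or ward-specific change.

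The figures assume one ward per step, 7 or 8 periods, equal ward sizes and an adoption order unrelated to ward rates. In fact, "The order in which clusters receive the intervention will be guided by logistical restrictions" and by clinicians' enthusiasm. Any confounding from that order is a separate matter which these rates do not include.

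**What to change.** Before analysis, name one primary model. The preferred form is logistic regression with ward effects, calendar-period effects, the intervention indicator, and either ward-period overdispersion or a ward-by-period random effect, tested against t on the ward-period residual degrees of freedom (about 35–41). Entering ward as a fixed effect also removes the between-ward comparison, which is useful when adoption order is not random.

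The simulated 3–8% is for the overdispersion form. If the random-effect form is chosen, check its error rate by simulation first. Moving the critical value from 1.96 to about 2.02 will not by itself bring 9.5% down to 5%.

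If GEE is kept as the primary method, require a Fay-Graubard or Mancl-DeRouen corrected sandwich with t on about 5 degrees of freedom (7 − 2). GEE need not be struck.

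The 33 months of pre-study data on six of the seven clusters can be used now to estimate ward-by-period variation, which would replace the assumed SDs above.

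The cost is analysis-plan wording and wider confidence intervals, hence less power than stated if wards do drift.

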## Results: pilot implementation

During a 6-week pilot period, participating clinicians honed the format of the HEADS-UP tool, ensuring it could be completed quickly and accurately. Subsequent iterations of the HEADS-UP tool incorporated further feedback from clinical staff and clinical governance teams on the content and use of the HEADS-UP briefing. This largely resulted in an increased focus on the outcomes of the briefing, namely the actions to be taken and which team member would be responsible for them.

The introduction of the tool was supervised initially by a physician researcher (SP). When led by a clinician, the HEADS-UP briefing typically took between 5 and 8 min to complete. Clinical teams’ use of the tool was deliberately unsupervised for the latter half of the pilot period, to gauge whether it was suitably concise and relevant to be used in practice without the presence of the researcher. The HEADS-UP briefing was completed unsupervised on 80% of working days. Taken together, these data suggest that the HEADS-UP trial is feasible.

## Trial status

Data collection is ongoing.

## Discussion

This stepped wedge cluster controlled trial will assess the impact of a simple intervention to improve quality and safety on medical wards. The design of the HEADS-UP tool, as well as its proposed implementation, intentionally minimises the disparity between the trial setting and daily clinical practice. This will make the study results immediately applicable to broad swathes of healthcare settings. We hope to obtain conclusive evidence for the success or failure of the intervention, but with a relatively prolonged data collection period, the study is prey to unanticipated systemic changes outside of our control. There is also a tension between effective HEADS-UP promotion, essential for adequate staff engagement, and contamination of the control groups. In addition, downstream interventions arising from the HEADS-UP process may impact multiple wards, regardless of their participation in HEADS-UP. The narrative record will help highlight where this may have been the case, and contextualise the impact of the tool.

In summary, HEADS-UP offers a novel, rapid whole-team analysis of clinical and administrative challenges, including adverse events, at ward level. This prospective trial will identify whether HEADS-UP is a useful addition to existing safety systems, and broader lessons for the implementation of safety and quality interventions within the complex medical ward environment.
